### Follow-up assessments

The first follow-up measure takes place after the MBCT training or the TAU-period. The MINI depression module is administered face-to-face or by phone and participants fill out the questionnaires either online or on paper. Participants are asked about changes in pharmacological or psychological treatment during the study period. Also participants deciding to discontinue MBCT are asked to participate in follow-up measures. In all MBCT completers (MBCT + TAU and participants of the TAU group who followed the MBCT after the TAU-period), the same follow-up measures are administered at three and six months after end of treatment. Due to logistic reasons it is not possible to keep assessors blind. To assess the inter-rater reliability of the MINI, all diagnostic interviews are audio taped and a randomly selected sample will be reassessed by an independent rater. For an overview of all measurement assessments see Table 1.

**Table 1 Tab1:** Overview of measures and corresponding measurement time points

Measure	Target concept	Baseline	FU1	FU2	FU3	FU4
IDS-SR	Depressive symptoms	●	●	●	●	●
MINI-depr. module	Diagnosis of major depression	●	●	●	●	●
WHOQOL-BREF	Quality of life	●	●	●	●	●
RRS-EXT	Rumination	●	●	●	●	●
FFMQ	Mindfulness skills	●	●	●	●	●
SCS	Self-compassion	●	●	●	●	●
MINI interview	Comorbid psychiatric disorders	●				
DM-TRD	Treatment-resistance	●				
CTQ	Childhood trauma	●				

*FU1:* 2 weeks post intervention (MBCT + TAU)/8-12 weeks post baseline (TAU), *FU2:* 3 months post intervention (MBCT+ TAU)/2 weeks post intervention (TAU), *FU3:* 6 months post intervention (MBCT + TAU)/3 months post intervention(TAU), *FU4:* 6 months post intervention (TAU)

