## Methods/Design

### Design

This study is a multi-center open-labeled randomized controlled trial with two groups: MBCT+ TAU vs. TAU. The study has been approved by the Medical Ethics Committee Arnhem-Nijmegen (nr. 2012/339) for all participating sites. Before randomization, written informed consent is obtained from all participants. Primary and secondary outcome measures are assessed at baseline and after MBCT + TAU (8–12 weeks) or after a TAU-period (8–12 weeks). Participants allocated to the TAU condition are offered participation in the MBCT after completion of the TAU-period and first follow-up assessment. Of all participants who completed the MBCT, follow-up measures take place at three and six months after the end of treatment. For an overview of the recruitment and measurement points see Fig. 1.

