### Procedure

**Assessment of eligibility, baseline measures and randomization**

All patients who indicated their interest in the study are invited for a research interview. Written informed consent is obtained during this first appointment. To assess eligibility and to classify comorbid psychiatric disorders, participants are interviewed by a research psychologist or psychiatrists in training with the depression, anxiety, psychosis and addiction modules of the Mini International Neuropsychiatric Interview (MINI; [25]). In addition, the following disorder-related characteristics are assessed: duration of current major depressive episode, number of psychological treatment sessions (i.e. CBT and/or IPT) during current major depressive episode, duration and doses of pharmacological treatments during the current depressive episode, number of depressive episodes during lifetime and age of onset. On the base of these details the research assistant fills out the Dutch Measure for quantification of Treatment Resistant Depression (DM-TRD, [26] [27]). After completion of the baseline questionnaires, a computer program is used to randomly allocate patients to either MBCT + TAU or TAU. A minimization strategy is used for severity of symptoms (IDS-SR ≥21 and ≤31 vs. > 31 and ≤ 39 vs. > 39) and duration of major depressive episode (1–2 years vs. > 2 years). If the period between randomization and start of the MBCT training exceeds four weeks in the MBCT + TAU condition, a repeated baseline assessment takes place.

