### Interventions

**MBCT + TAU**

The MBCT consists of eight weekly sessions of 2.5 h in groups of 8–15 patients and one additional day of silent practice between the 5^th^ and 7^th^ session. Participants are asked to do daily homework assignments. MBCT combines mindfulness meditation techniques, as sitting meditation and the body scan with elements of cognitive therapy such as psycho education and the identification of automatic negative thoughts. The MBCT manual described by Segal, Williams and Teasdale [13] is used. Participants are enrolled in regular MBCT trainings provided at the Radboudumc Centre for Mindfulness and Pro Persona for (remitted) depressed patients. This means that the training groups not only consist of study participants but also of regular patients with a wide range of depressive symptoms.

MBCT trainings are taught by experienced mindfulness trainers who completed a 2-year post-graduate teacher training program at the Radboudumc Centre for Mindfulness. With this, they all meet the training criteria described in the MBCT good practice guidelines (UK Mindfulness-Based Teacher Trainer Network, 2011). Two MBCT sessions of each trainer are videotaped to verify adherence to the MBCT protocol. In addition to MBCT the participants receive TAU.

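### FU1, the primary endpoint visit, is timed from the end of the course in MBCT + TAU but from baseline in TAU, so time since randomisation can differ by arm

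*Protocol article*

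**What the plan says.** - **Timing of FU1.** The Table 1 footnote (Follow-up assessments) puts FU1 at "2 weeks post intervention (MBCT + TAU)/8-12 weeks post baseline (TAU"). The text of the same section says only that "The first follow-up measure takes place after the MBCT training or the TAU-period".
- **Design section.** Outcomes are taken at baseline and "after MBCT + TAU (8–12 weeks) or after a TAU-period (8–12 weeks"), the same span for both arms.
- **Course.** Under Interventions, "The MBCT consists of eight weekly sessions of 2.5 h". Study participants join the regular courses at the sites, so start dates follow the course calendar.
- **Wait.** Randomisation comes after the baseline questionnaires, so baseline and randomisation are close in time. The section on eligibility, baseline and randomisation then provides: "If the period between randomization and start of the MBCT training exceeds four weeks in the MBCT + TAU condition, a repeated baseline assessment" is made. It states no maximum wait and no repeated baseline in the TAU arm.
- **Primary analysis.** A general linear model of FU1 depressive symptoms on condition and baseline score. It has no term for time.

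**The concern.** The two arms run on different clocks. In TAU the interval from randomisation to FU1 is fixed at 8–12 weeks. In MBCT + TAU it is the wait for a course, plus the course, plus two weeks. If waits are often more than two or three weeks, the MBCT + TAU arm is systematically assessed later. Whatever happens in the extra weeks, such as natural course, regression to the mean after entry on IDS-SR ≥ 21, or changes in other treatment (which participants are free to make), then falls in one arm only.

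Adjusting for baseline score does not remove this, because the difference goes with the arm and not with the baseline level. It would be read as part of the MBCT effect in the primary comparison and in the secondary comparisons at FU1.

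**Working it through.** **The plan's own sample size.** Inputs from Power analysis and sample size: d = 0.53, baseline–follow-up correlation 0.5, alpha 0.05 (taken as two-sided), power 80%.

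n per arm = 2(1 − 0.5²)(1.960 + 0.842)² / 0.53² = 41.9 by the normal approximation and 42.9 with the t distribution, so 43. Then 2 × 43 + 8 = 94. The figure reproduces and is not in dispute; 0.53 serves below only as a yardstick.

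**Weeks from randomisation to FU1 in MBCT + TAU.** Time = wait + course + 2. The course is 7 weeks from first to last session, or 8 if counted as full weeks. The waits are assumptions, since the article gives no distribution. The last column runs from (earliest MBCT + TAU date − 12) to (latest MBCT + TAU date − 8).

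| Wait (weeks) | FU1 in MBCT + TAU | FU1 in TAU | Difference for individual pairs |
|---|---|---|---|
| 0 | 9–10 | 8–12 | −3 to +2 |
| 2 | 11–12 | 8–12 | −1 to +4 |
| 4 | 13–14 | 8–12 | +1 to +6 |
| 6 | 15–16 | 8–12 | +3 to +8 |

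FU1 passes week 12 when wait + 9 > 12 or wait + 10 > 12, that is, when the wait exceeds 3 or 2 weeks. A four-week wait, which triggers no repeated baseline, is already outside the TAU window.

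**Mean gap between arms.** The bias depends on the difference in mean timing, not on the extreme pairs. Take TAU as uniform over 8–12 weeks (mean 10) and course + 2 as 9.5 on average.

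- Waits uniform over 0–4 weeks (mean 2): 9.5 + 2 − 10 = 1.5 weeks.
- All waits 4 weeks: 9.5 + 4 − 10 = 3.5 weeks.

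**Possible bias.** Bias = drift × mean gap. Drift of 0.01–0.03 SD per week is an assumption; the article gives no rate of change for the IDS-SR.

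- Gap 1.5: 0.015–0.045 SD; divided by 0.53, 3–8%.
- Gap 3.5: 0.035–0.105 SD; divided by 0.53, 7–20%.

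**Does the repeated baseline help?** It applies only above four weeks and only in MBCT + TAU. It shortens the interval from the latest baseline to FU1, but not the interval from randomisation to FU1. It is also measured after allocation is known. The article does not say which baseline enters the model. If the first is used, the wait remains inside the comparison. If the repeat is used, the covariate is measured differently in the two arms: a fall in scores between the two baselines would be adjusted away in one arm only, which works against MBCT.

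**The case against.** The best defence is that equal periods were plainly intended. The Design section gives both arms 8–12 weeks, and with a wait of up to about two weeks the MBCT + TAU visit does fall inside that window. Waits over four weeks are provided for as a possibility, not forecast. For those patients a repeated baseline near course start would bring baseline-to-FU1 back to about 9–10 weeks. Drift may also be small: every participant has been depressed for at least 12 months, and the Background reports that recovery virtually stagnates after a year. Finally, a scheduling rule for TAU visits is something a full protocol may contain and an article may omit.

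Much of this stands. It limits the size of the problem and rules out calling the gap certain. It does not remove the point. The article does not merely leave the schedule out; it states two that agree only when waits are short. The repeated baseline acts in one arm only and leaves time since randomisation untouched.

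A reader might infer a much larger bias by setting the latest MBCT + TAU date against the earliest TAU date, a 6-week gap at a four-week wait. At 0.03 SD per week that gives 0.18 SD, or 34% of 0.53. The documents do not support this as an arm-level figure: a mean gap of 6 weeks needs an average wait of 10 + 6 − 9.5 = 6.5 weeks, and nothing suggests that.

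**Conclusion.** The concern holds as a conditional one and should be fixed. The anchors for FU1 differ by arm, the Design section and the Table 1 footnote agree only if courses start within about 2–3 weeks of randomisation, and the primary model would assign any systematic timing difference to condition.

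The size cannot be computed from the document. Under the assumed drift and mean gaps of 1.5–3.5 weeks it is about 0.015–0.105 SD, or 3–20% of the planned effect, with the low end more plausible.

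A reader might also infer that the bias must favour MBCT. That does not follow. Background improvement with the first baseline as covariate would favour it; background worsening, or use of the repeated baseline as covariate, could work the other way. Both arms may change treatment, possibly because of worsening. The sample size calculation is unaffected.

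**What to change.** 1. At randomisation, set each TAU participant's FU1 to the FU1 date of the MBCT course that he or she would have joined at that site. Time since randomisation then has the same planned distribution in both arms.
2. Reconcile the Design section and the Table 1 footnote with that rule.
3. State that the pre-randomisation baseline is the covariate in both arms, and keep any repeated baseline as descriptive.
4. Report weeks from randomisation to FU1 by arm.
5. For participants already assessed, present any timing-adjusted analysis only as a labelled sensitivity analysis, because FU1 time is largely determined by arm. Do not restrict to participants with overlapping FU1 times: that selects on a post-randomisation variable and would drop long-wait MBCT + TAU patients.

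The cost is a scheduling rule and a small amendment, with no extra visits. The downside is that FU1, and the offer of MBCT that follows it, comes somewhat later for some TAU participants.

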### Interventions

**MBCT + TAU**

The MBCT consists of eight weekly sessions of 2.5 h in groups of 8–15 patients and one additional day of silent practice between the 5^th^ and 7^th^ session. Participants are asked to do daily homework assignments. MBCT combines mindfulness meditation techniques, as sitting meditation and the body scan with elements of cognitive therapy such as psycho education and the identification of automatic negative thoughts. The MBCT manual described by Segal, Williams and Teasdale [13] is used. Participants are enrolled in regular MBCT trainings provided at the Radboudumc Centre for Mindfulness and Pro Persona for (remitted) depressed patients. This means that the training groups not only consist of study participants but also of regular patients with a wide range of depressive symptoms.

MBCT trainings are taught by experienced mindfulness trainers who completed a 2-year post-graduate teacher training program at the Radboudumc Centre for Mindfulness. With this, they all meet the training criteria described in the MBCT good practice guidelines (UK Mindfulness-Based Teacher Trainer Network, 2011). Two MBCT sessions of each trainer are videotaped to verify adherence to the MBCT protocol. In addition to MBCT the participants receive TAU.

### TAU

TAU may consist of any treatment the participant or current mental health care specialist sees as necessary. Participants are encouraged to continue treatment they followed prior to enrolling in the study. The number of treatment sessions and use of antidepressant medication are recorded.

### Measurements

#### Primary outcome measure

### Depressive symptoms

The primary outcome measure is the level of depressive symptoms measured with the Inventory of Depressive Symptomatology Self-Report (IDS-SR). The IDS-SR is a 30-item self report questionnaire and has good psychometric properties [28]. The IDS-SR has previously been used in research on MBCT in depression and has been shown to be sensitive to change [17].

#### Secondary outcome measures

### Remission rates

Remission from depression according to DSM-IV criteria is assessed with the major depression module of the Mini International Neuropsychiatric Interview (MINI; [25]).

### Quality of life

Perceived quality of life is measured using the 26 -item World Health Organization Quality of Life scale (WHOQOL-BREF; [29]). Psychometric properties were tested in a sample of Dutch psychiatric outpatients and are considered to be good [30].

### Rumination

Rumination is measured with the extended version of the Ruminative Response Scale (RRS-EXT [31, 32]. The RRS-EXT distinguishes between a more reflective way of thinking (i.e. reflective pondering) and a more maladaptive way of thinking about symptoms (i.e. brooding) [33].

### Mindfulness skills

Mindfulness skills are measured with the Five Facets Mindfulness Questionnaire (FFMQ. [34]. The FFMQ consists of 39 items which are divided in five subscales: observing, describing, acting with awareness, non-judging of inner experience and non-reactivity of inner experience. The Dutch version of the FFMQ has good psychometric properties [35, 36] and has previously been used in research on mindfulness skills in bipolar disorder [37].

### Self-compassion

Self-compassion is assessed with the Self Compassion Scale (SCS; [38, 39]). The SCS is an 26-item self report measure and consists of six components: self-kindness, self-judgment, common humanity, isolation, mindfulness, and over-identification. The scale has good psychometric properties and high scores on the SCS are related to psychological well-being [39].

#### Possibly moderating variables

### Treatment-resistance

The Dutch Measure for quantification of Treatment Resistant Depression (DM-TRD; [26, 27]) is used to investigate treatment-resistance of the current depressive episode. With the DM-TRD several dimensions of treatment-resistance are scored by the clinician (duration, symptom severity, functional impairment, comorbid anxiety symptoms, prosocial stressors, treatment failures of pharmacological and psychological treatment) which leads to a total score ranging from 2–26.

### Childhood trauma

To assess the experience of traumatic childhood events, participants fill out the Childhood Trauma Questionnaire (CTQ-SF; [40]). This 28-item questionnaire measures traumatic experiences and maltreatment during childhood. The CTQ-SF has previous been validated in a Dutch clinical sample [41].

### Data handling

All study-related information is stored in secure folders with limited access. Paper-based data collection forms only contain participant numbers to maintain participant confidentiality and are stored in a locked cabinet in an area with limited access. Electronic data files are password protected. The list linking participant number and personal information is stored in a separated password protected file. Paper-based data entry will be double checked. Data will be stored for 15 years after the end of inclusion. The study has low to negligibly risks therefore no data monitoring committee is assigned. Only the first author and principal investigators or persons assigned by them will have access to the final data set. Authors of the final trial report will have made substantial contribution to the design, conduction, interpretation and reporting of the trial. We will not use professional writers. Study results will be presented via publications and presentations; study participants, funders and involved clinicians will receive a summary of the study results.

### Statistical analyses

**Power analysis and sample size**

A power analysis was executed based on the findings of van Aalderen et al. [20]. Van Aalderen and colleagues [20] reported an effect size of 0.53 (Cohen’s *d*) in a sample of 69 currently depressed patients. Based on an alpha of 0.05 and power of 80 %, estimating the correlation between baseline and first follow-up measurements to be 0.5 and intending to use an ANCOVA controlling for baseline levels of depression, a needed sample size of 43 per condition was calculated. Expecting a drop-out of 8 patients, a total of 94 participants will be recruited.

### Analyses plan

The MBCT + TAU and TAU conditions will be compared on baseline sample characteristics to ensure that all possible meaningful characteristics were evenly distributed across the conditions. To examine treatment outcome, we will use both intention-to-treat and per-protocol samples. Participants are considered completers of the MBCT if they attend at least four sessions of MBCT. To examine whether effects for participants experiencing a depressive episode for one to two years and participants meeting criteria for chronic depression according to the DSM-IV (≥2 years) are different, the primary and secondary analyses will be repeated in these subgroups.

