### Primary analysis

The effect of condition (MBCT + TAU vs. TAU) on the primary outcome measure (depressive symptoms) will be examined using general linear models. Condition and baseline score of depressive symptoms will be included as independent variables, depressive symptoms at FU1 as the dependent variable. Because MBCT is delivered in mixed groups consisting of regular patients and a few study participants and previous studies did not yield an effect of therapy group [20], we will not incorporate a random group effect.

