### Secondary analyses

Effects on quality of life, rumination, mindfulness skills, and self-compassion will also be investigated using general linear models with the same independent variable as in the primary analysis. To investigate effects on remission rates a χ^2^ test will be performed. Moderating effects of level of treatment-resistance and childhood trauma will be investigated by including an interaction effect (condition*moderator) in the models. Furthermore, exploratory analyses on rumination, mindfulness skills and self-compassion as possible underlying mechanisms of change will be conducted. Consolidation and moderation of treatment effect will be investigated in the whole sample of MBCT completers (MBCT + TAU and TAU) using end-of-treatment assessments and follow-up assessments at three and six months after end of treatment.

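### The plan asks whether the MBCT effect differs by episode duration, but only repeats the analyses within each duration subgroup and names no test of the difference

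*Protocol article*

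**What the plan says.** The Analyses plan section gives the purpose of the duration comparison: "To examine whether effects for participants experiencing a depressive episode for one to two years and participants meeting criteria for chronic depression" (two years or more under DSM-IV) are different. The method follows in the same sentence: "the primary and secondary analyses will be repeated in these subgroups". No interaction term or other direct comparison is named for duration.

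The analysis to be repeated is the ANCOVA under Primary analysis: "Condition and baseline score of depressive symptoms will be included as independent variables, depressive symptoms at FU1 as the dependent variable". The continuous secondary outcomes use the same kind of model, and remission is compared with a chi-square test.

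Under Secondary analyses, two other baseline variables are handled differently: "Moderating effects of level of treatment-resistance and childhood trauma will be investigated by including an interaction effect (condition*moderator) in the models". Duration is not in that list, although it is a minimisation factor: "duration of major depressive episode (1–2 years vs. > 2 years".

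**The concern.** The method does not answer the question it is attached to. Fitting the model separately in two subgroups gives two effects, each tested against no effect. Whether the effects differ from each other depends on the difference between them and its standard error, which neither fit supplies. With identical true effects, one subgroup can reach significance and the other miss it simply because each holds only part of a sample sized for one overall comparison.

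At stake is a possible statement that MBCT works in episodes of one to two years but not in DSM-IV chronic depression, or the reverse, without evidence of a difference. Because patients are admitted from 12 months, readers will want to know whether the result carries over to the DSM-IV chronic group. The interaction planned for the treatment-resistance score does not fill the gap: duration is only one of several dimensions of that score, so its interaction does not test the two-year contrast.

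**Working it through.** **Inputs (Power analysis and sample size).** The source study "reported an effect size of 0.53" (Cohen's d). The correlation between baseline and first follow-up is 0.5. "Based on an alpha of 0.05 and power of 80"% gives the error rates. There are 43 per condition, so 86 analysed, plus 8 expected dropouts = 94 recruited. Sidedness is not stated.

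**Reproducing the plan's figure.** The residual SD after baseline adjustment is sqrt(1 − 0.5²) = 0.866. With n per arm, the noncentrality is d / (0.866 × sqrt(2/n)) on 2n − 3 degrees of freedom. For n = 43 this is 0.53 / 0.187 = 2.84, which gives two-sided power of 80.1%; n = 42 gives 79.1%. So 43 is reproduced with a two-sided 5% test. By the normal approximation, a one-sided test would need 34 per arm and no baseline adjustment would need 56; neither fits.

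**Equal true effects, tested separately.** Assume d = 0.53 in both subgroups, equal arms within each subgroup and 86 analysed. If the subgroup powers are p1 and p2, the chance that exactly one subgroup is significant is p1(1 − p2) + p2(1 − p1). The subgroup split is my assumption.

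| Split | n per arm | Power in each | Exactly one significant |
|---|---|---|---|
| 50/50 | 21.5 and 21.5 | 49.9%, 49.9% | 50.0% |
| 40/60 | 17.2 and 25.8 | 41.3%, 57.7% | 51.3% |
| 30/70 | 12.9 and 30.1 | 31.9%, 64.6% | 55.3% |
| 20/80 | 8.6 and 34.4 | 22.0%, 70.6% | 61.5% |

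For example, at 30/70: 0.319 × 0.354 + 0.646 × 0.681 = 0.113 + 0.440 = 0.553. With all 94 analysed, the 50/50 figure is 49.7%. A simulation of the ANCOVA (4,000 trials per split, N = 86) gave 50.6% at 50/50 and 56.2% at 30/70.

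**Dependence on the common true effect (50/50, N = 86).**

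| True d in both subgroups | 0 | 0.2 | 0.3 | 0.4 | 0.53 | 0.7 | 0.8 | 1.0 |
|---|---|---|---|---|---|---|---|---|
| Exactly one significant | 9.5% | 20% | 32% | 43% | 50% | 39% | 27% | 8% |

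The value at d = 0 is 2 × 0.05 × 0.95 = 0.095.

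**Interaction test on the same data.** In the same simulations, a condition by duration term was significant at 5% in 4.6% of trials (50/50) and 5.5% (30/70), close to the nominal rate.

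**Precision of the interaction.** SE = sqrt(0.75 × (4/N1 + 4/N2)), where N1 and N2 are the subgroup totals.
- 50/50: sqrt(0.75 × (4/43 + 4/43)) = 0.374, twice the main-effect SE of sqrt(0.75 × 2/43) = 0.187. The difference detectable with 80% power is 2.80 × 0.374 = 1.05 SD.
- 30/70: sqrt(0.75 × (4/25.8 + 4/60.2)) = 0.408, so 2.80 × 0.408 = 1.14 SD.
- Power for a difference of 0.53 SD is about 29% at 50/50 and 25% at 30/70.

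**The case against.** **No decision rule is stated.** The protocol does not say that a difference will be declared when one subgroup is significant and the other is not. The subgroup models also yield estimates and intervals that could be compared properly. This stands. A reader might infer that the trial would report a false contrast; the text supports only that the plan names no direct comparison and so leaves that inference open.

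**The one-in-two figure is conditional.** A reader might take it as a general property of the plan. It is not: it needs a common effect near 0.53, an assumed split and the discordance reading above. At 50/50 it falls to 20% at d = 0.2 and 8% at d = 1.0.

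**Secondary outcomes.** Because the repetition covers them too, it is tempting to say that false contrasts are likely across the board. The protocol gives a planning effect and correlation for depressive symptoms only, so no figure can be put on this.

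**The comparison is ancillary.** The Aims section names treatment-resistance and childhood trauma as possible modifiers, not duration, and both of those receive an interaction term. The primary model, sample size and primary conclusion are untouched. This limits the severity, but does not make the stated method fit its question.

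**An interaction test has little power here.** True. That is a reason to report an imprecise estimate with its interval, not to leave the difference unestimated.

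**Cut-points.** Minimisation puts the upper stratum above two years, while the subgroup starts at two years. They differ only for a patient at exactly two years. This is an editorial inconsistency and adds no weight to the main point.

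**Conclusion.** The point holds in a limited form. The plan poses a question about a difference in effects and attaches a method that does not estimate or test that difference, although it uses the right method for two other modifiers. If discordant significance were taken as evidence, equal true effects at the planning values would look different in about 50% of trials at an even split and 55% to 62% at 30/70 to 20/80, against about 5% for an interaction test. These figures rest on d = 0.53 in both subgroups, a correlation of 0.5, two-sided 5% tests, 86 analysed, balanced arms within subgroups and assumed splits.

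This should be corrected before analysis. It is not critical, because it concerns an ancillary comparison and leaves the primary analysis as it is.

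**What to change.** Replace the sentence in the Analyses plan section with wording such as: *Whether effects differ by episode duration will be judged from a condition by duration term added, with the duration main effect, to the full-sample linear models. For remission an equivalent test will be used, such as a logistic model with the interaction or a test of homogeneity of odds ratios. The interaction estimate and 95% CI will be reported and labelled exploratory. Estimates within duration subgroups are descriptive only.*

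Remission needs its own clause because its planned chi-square test has no model to which a term can be added.

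Reconcile the two-year boundary between the randomisation and analysis sections. The minimisation cut should not be imposed by default, since the question is framed around DSM-IV chronicity.

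The cost is a sentence or two and no new data, as duration is already collected. The downside is imprecision: with detectable differences of about 1.05 to 1.14 SD, the interaction will rarely settle the question. It guards against an unsupported claim, and a non-significant result must not be read as evidence that the effects are equal.
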